### Safety: AUDIT-C, DAST-10, and SDS-C

During the treatment period, we also want to confirm that the VR-CBT is a safe pretreatment and want to observe a potential increase in the use of alcohol and drugs during the therapy. This will be done using presession evaluations with AUDIT-C, DAST, and SDS-C with a 1-week time frame. The AUDIT-C assesses alcohol consumption and drinking behaviors using 3 items [42]. The full AUDIT with 10 items has been translated and validated. Both the English and French versions of AUDIT have favorable psychometric properties, including high sensitivity and specificity (approximately 90%), and this also concerns the AUDIT-C [75-77].

The DAST is a 10-item validated self-report scale that will be used to screen for and assess drug use over the previous 12 months [41,78]. Typically, the DAST-10 achieves a sensitivity of 41% to 95% and a specificity of 68% to 99%, depending on the population and diagnostic information used [78]. No information is yet available about the validity of the French translation of the DAST.

The SDS-C[43] consists of 5 items with good internal reliability and discriminant validity, with a cutoff score of 4 [79]. No information is yet available about the validity of the French translation of the Severity of Dependence Scale [80].

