### Participants

#### Sampling

Our primary *inclusion criteria* are that the participants must (1) self-identify as Inuk, (2) live in the city where the study is taking place, (3) be aged between 14 and 60 years of age, and (4) be proficient in English or French.

With exclusion criteria, we confirm safety and best fit with the study necessitating VR and psychophysiological equipment use. We exclude those who do not identify as Inuk, youth aged <14 years, and adults aged >60 years, as well as individuals who do not tolerate VR headset and study sensors. We exclude individuals with a self-reported history of psychosis or schizophrenia, with current substance abuse as measured by screens (score >8 on the Alcohol Use Disorders Identification Test C (AUDIT-C) or >3 on the Drug Abuse Screen Test), or with any change in psychoactive medications 4 weeks before screening. In addition, we exclude individuals with physical conditions that might cause risks during VR use (ie, history of cardiac condition or epilepsy). There are no exclusions based on other concomitant care.

Meeting the diagnostic criteria for any specific disorder, verified history of trauma, or trauma symptoms was not part of our inclusion and exclusion criteria, given our focus on cultural sensitivity, our chosen skills-building approach in the therapy manual, and the shared history of trauma by community members.

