#### Sample Size

There is, to our knowledge, no estimate of the effect size of emotion regulation–based VR interventions among Indigenous populations, and this proof-of-concept study will be necessary for accurate estimation of power in future trials. As described in the previous section, mental health risks among Indigenous and Inuit populations differ from those among the general population, which emphasizes the need for this proof-of-concept study specifically in this population for power calculations in future work. However, a previous VR intervention for anxiety disorders among a general population sample had an estimated effect size of g=0.78 (medium) compared with minimal-attention controls and g=0.90 (large) with no-treatment controls [26,27]. To attain statistical power >90% with an alpha of *P*<.5, the sample size of n=20 in the active treatment group and n=20 in the active control group is sufficient for generalized linear models with a similar effect size (power=0.97; *df*=38; *P*=.05).

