##### CORE-OM, 10-Item Version

The CORE is widely used as an outcome measure in psychotherapy and has several versions, including the CORE-OM and the 10-item version CORE-10 [30,31]. The CORE-OM and CORE-10 are screening measures for psychological distress, including items for well-being, psychological symptoms, functioning, and risk. The CORE-OM has excellent internal consistency in clinical samples (α=.94) and for each of its subscales (α=.75-.94); it also has good test-retest reliability (*P*=.83) [73]. The CORE-10 with a cutoff score of 11 differentiated between clinical and nonclinical general samples with a sensitivity of .85. Its internal consistency was α=.90, and it had a reliable change index of 6 points [30]. The widely accepted French translation had validity results forthcoming from the University of Toulouse [74].

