### Strengths and Limitations

The process of cultural adaptation of psychotherapy was conducted to increase acceptance. The advisory committee recommended study inclusion based on sociocultural background, not trauma symptoms, to improve the cultural safety of the trial. Accordingly, inclusion is based on subjective motivation for improved mental health rather than any categorical diagnosis or subjective or objective need for treatment. In addition, the content of the psychotherapy was modified to confirm safety, according to the comments from the advisory committee. These modifications include reducing exposure and distress-producing exercises and removing the homework normally part of the therapy. A limitation is that these changes may challenge the odds of a psychotherapeutic response.

In our study protocol, we included an active control group, noting the vulnerability of the study population; this may lead to reduced between-group effects. However, only the active treatment is culturally adapted and guided by a psychotherapist, which could improve attendance and thus long-term efficacy in the active treatment group. We will observe the impact of the setting as compared with the content on acceptance while asking for the preference for therapist-guided or self-management treatment. This proof-of-concept RCT will inform us about the potential challenges or limitations of the study protocol, and we can characterize the best outcome measures and calculate power for the further efficacy trial. We consider the scientific risks acceptable, given the extreme imbalance between the need and availability for access to valid and safe treatments.

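### Substance-use scores in about 20 treated people cannot confirm that VR-CBT is safe; the safety aim should be to describe harms in both arms

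*Protocol article*

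**What the plan says.** The section *Safety: AUDIT-C, DAST-10, and SDS-C* gives a two-part aim. The first part is "we also want to confirm that the VR-CBT is a safe pretreatment"; the second is that the team "want to observe a potential increase in the use of alcohol and drugs during the therapy". The means follow at once: "This will be done using presession evaluations with AUDIT-C, DAST, and SDS-C with a 1-week time frame". The section gives no criterion, margin or event definition for safe.

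*Sample Size* says that "the sample size of n=20 in the active treatment group and n=20 in the active control group is sufficient". That number is argued from efficacy effect sizes only.

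Other sections name other kinds of harm:

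- *Sampling*: "we exclude individuals with physical conditions that might cause risks during VR use"; people who cannot tolerate the headset or sensors are also excluded.
- *Objective Measures*: the height exercise can be shortened or abandoned because of distress.
- *Feasibility: Attrition and Adherence*: participants judged to be at risk may be withdrawn.
- *Strengths and Limitations*: the therapy was changed for safety. "These modifications include reducing exposure and distress-producing exercises".

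Psychological state is measured. GAD-7, PHQ-9, PC-PTSD-5 and the CORE scales, which include risk items, are on the baseline list. The questionnaires are repeated at weeks 10 to 11 and at week 22. *Analyses for Rating Scales* plans to describe changes in mood, anxiety and trauma symptoms by condition. For the CORE-10 the article reports that "it had a reliable change index of 6 points".

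**The concern.** The aim is general (the therapy is safe), while the instruments attached to it cover one domain (alcohol, drugs and cannabis) in a group sized for something else. The harms that the protocol itself anticipates from a VR-based psychotherapy are mainly distress, psychological worsening and intolerance of VR, and none of these is linked to the safety aim.

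At stake is what the report may say. If drinking and drug scores stay level, the text as written invites a statement that safety was confirmed. The data could not support that statement, and it would concern a population that the protocol calls vulnerable.

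**Working it through.** **No safety figure to reproduce.** The only power figure in the article (0.97) is for efficacy. It plays no part in this point.

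**Inputs.** VR-CBT participants: n = 20 (*Sample Size*). CORE-10 reliable change index: 6 points (*CORE-OM, 10-Item Version*). True harm rates below are assumed for illustration, because the article gives none.

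**1. What zero events in one arm can rule out.** With 0 events in n people, the exact upper limit for the true rate is 1 − a^(1/n), where a = 0.025 for a two-sided 95% interval and a = 0.05 for a one-sided bound.

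- Two-sided: 1 − 0.025^(1/20) = 0.168, or 16.8%.
- One-sided: 1 − 0.05^(1/20) = 0.139, or 13.9%.
- If only 14 people were evaluable (an assumption, not a figure from the article): 1 − 0.025^(1/14) = 0.232 two-sided and 1 − 0.05^(1/14) = 0.193 one-sided.

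**2. Chance of missing a harm entirely.** P(0 events in 20) = (1 − p)^20.

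| Assumed true rate p | P(no event seen) |
|---|---|
| 1% | 0.99^20 = 82% |
| 5% | 0.95^20 = 36% |
| 10% | 0.90^20 = 12% |

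**3. Size needed for a clean result to mean something.** For zero events to give a one-sided 95% bound below u, n must be at least ln(0.05)/ln(1 − u). That is 29 people for u = 10%, 59 for 5% and 299 for 1%.

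**4. Precision of the scale scores themselves.** AUDIT-C, DAST and SDS-C are scores, so the zero-event bounds do not apply to them directly. With 20 per arm, the 95% half-width for a mean is t(0.975, 19)/√20 = 0.47 SD within an arm. For a difference between arms it is t(0.975, 38) × √(2/20) = 0.64 SD. A level average would therefore leave a moderate rise in use open, even within the one domain that these scales cover.

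**5. Whether the data for a better summary exist.** *Week 0: Baseline Measurement* lists the CORE-10, *Week 10 to 11* repeats the questionnaires, and *Week 22* repeats all baseline questionnaires. A count of people who worsen by 6 points or more can therefore be made in both arms at two times. It should stay descriptive: for assumed worsening rates of 10% and 30%, 20 per arm gives about 35% power.

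**6. What the data do not cover.** Reactivity testing is repeated only in people with at least 7 sessions, so early leavers are absent from the second test. Calm Place is used at home, and the article describes no record of VR sessions that were stopped for distress there.

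**The case against.** The strongest reply is that the verb is used loosely. In *Sampling* and in *Strengths and Limitations* the authors use it to mean ensure, and in the safety section it stands beside an aim to observe substance use, which is monitoring. No hypothesis, margin or decision rule is attached, and safety is not among the aims in *Research Aims*. This softens the point, and it means that no formal safety test is being claimed. It does not remove the point, because here the verb is followed by a measurement plan and so reads as a conclusion to be drawn from data. If that plan belongs only to the substance-use half of the sentence, the general aim has no named instrument at all.

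A reader might go further and infer that the trial leaves out psychological harm. The article does not support that. Depression, anxiety, PTSD symptoms and CORE risk items are collected in both arms at three times, symptom change is to be described, anxiety and arousal are rated after each reactivity segment, reasons for dropout are recorded when possible, and Calm Place participants are contacted weekly about safety. What remains is that none of this is named as a safety outcome.

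A reader might also infer that adverse events will not be collected, or that a safety verdict will pass to the larger trial. The first may sit in the full protocol, which is not shown. On the second, the article names outcome measures, power calculations and preferences as what carries forward. Neither belongs to this point.

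It is also true that the CORE-10 index is quoted as a psychometric property, and that not using it to count worsening is no error. It is proposed because it is already in the article and costs nothing to apply.

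**Conclusion.** The stated aim is stronger than the design can deliver. Substance-use scores in about 20 treated people cannot support a general conclusion that VR-CBT is safe. Zero events in 20 is compatible with a true rate of up to 16.8% (two-sided) or 13.9% (one-sided), and a 5% harm would be missed entirely 36% of the time. These figures assume that all 20 are observed and that a harm can be counted as present or absent; fewer evaluable people widen the bounds.

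The point is limited to the claim and to which outcomes carry it. Psychological symptoms are measured and described, but they are not tied to the safety aim. The correction is cheap and changes what the trial can legitimately conclude about safety.

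**What to change.** In the safety section, replace "we also want to confirm that the VR-CBT is a safe pretreatment" with: *describe harms in both arms; the study is too small to establish safety*. The substance-use scales can stay as one part of that description.

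Then name a safety summary, by randomised arm and with exact 95% confidence intervals:

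- the number of participants whose CORE-10 worsens by at least 6 points from baseline to weeks 10 to 11, and from baseline to week 22, with the number assessed at each time;
- the number withdrawn because they were judged to be at risk.

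Reactivity segments stopped for distress can be reported descriptively, with a note that the post-treatment test covers only people with at least 7 sessions. Home VR sessions stopped for distress would need a small log field and should not be presented as data already in hand.

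The cost is a change of wording, one extra descriptive table and a more modest safety statement. The CORE-10 counts need no new measure or visit.

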### Data Analysis

#### Analyses for Rating Scales

Expecting nonnormally distributed data in a small human sample, we will conduct nonparametric tests and generate descriptive and comparative statistics to detect between-group differences for the 2 conditions, VR-CBT (A) and Active Control VR program (B), using R Statistical and Computing Software (R Core Team). We will use generalized mixed linear models to compare the 2 conditions using scores on DERS-16 across several time points (pre- and posttreatment as well as biweekly and bimonthly time points). In addition, we will describe changes in mood, anxiety, and trauma symptoms for the 2 conditions (pre- and posttreatment, as well as biweekly and bimonthly time points). The data collection for time points varies based on the administration instructions for each scale (weekly, biweekly, monthly, etc). Cohen *d* or nonparametric tests will calculate the effect size between the 2 conditions.

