#### Translation

A professional translator translated each of the self-reported measures that did not have the existing French versions. For comparability, given the small sample size, the surveys will be administered in either English or French for data collection, and the language controlled for in statistical analysis. However, each psychometric measure was translated to Inuktitut to complement the understanding of English and French surveys.

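### The DERS-16 analysis lists pretreatment as an outcome time point without naming the treatment contrast, and states no use of the baseline score for adjustment

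*Protocol article*

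**What the plan says.** Under Analyses for Rating Scales, the protocol article states: "We will use generalized mixed linear models to compare the 2 conditions using scores on DERS-16 across several time points (pre- and posttreatment", and the parenthesis goes on to biweekly and bimonthly points. Pretreatment is thus one of the time points at which the outcome enters the model. The sentence names no condition main effect, no condition-by-time term and no contrast at a given visit.

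The same section closes with the effect size: "Cohen *d* or nonparametric tests will calculate the effect size between the 2 conditions". No adjustment is attached to it.

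The one adjustment variable that the article names is in the Translation section, where the survey language is to be recorded "and the language controlled for in statistical analysis". The baseline measurement section (Week 0) lists the DERS-16 among the scales taken before the intervention, so every randomised participant should have a baseline score. The Sample Size section argues from a two-group comparison that 20 per arm "is sufficient for generalized linear models with a similar effect size".

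**The concern.** The question for this scale is whether emotion regulation after treatment differs between VR-CBT and Calm Place. The sentence allows several tests that answer this with very different precision: a comparison averaged over all time points, a condition-by-time contrast, or a difference at posttreatment. The effect size that will be reported is, as written, a raw difference between the conditions.

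Baseline matters more than usual here. Eligibility sets no symptom threshold, so baseline scores may vary widely. Randomisation is simple 1:1. With 20 per arm the standard error of the baseline difference is sqrt(2/20) = 0.32 SD, so a chance imbalance above 0.3 SD in either direction occurs about 34% of the time (normal approximation). An unadjusted effect size carries part of that imbalance into the estimate. The article says that the trial's data will guide the choice of primary outcome and the power calculation for a larger trial, so the precision of this estimate has a use beyond the present test.

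**Working it through.** **Inputs from the article.** 20 per arm. For the effect size, a cited VR intervention "had an estimated effect size of g=0.78 (medium) compared with minimal-attention controls and g=0.90 (large) with no-treatment controls"; 0.78 is used because the article describes Calm Place as a minimal-attention control. The article gives no pre-post correlation r for this trial. It cites a retest reliability of 0.88, which is best read as an upper end.

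**Assumptions.** r of .5, .7 and .8; unit SD at every visit; no dropout; two-sided 5%. Power is from the noncentral t with noncentrality d × sqrt(20/2), on 38 degrees of freedom (37 with a covariate).

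**The plan's own figure.** The Sample Size section reports "power=0.97; *df*=38; *P*=.05". A two-group comparison at two-sided .05 gives 0.67 for 0.78 and 0.79 for 0.90, so 0.97 is not reproduced. The same section also prints "To attain statistical power >90% with an alpha of *P*<.5"; with alpha of .5 taken literally, power is 0.964 and 0.985. That inconsistency is a separate matter. For the present point, 0.67 is the reference value for an unadjusted comparison.

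**Standardised effect under each analysis.**
- Unadjusted posttreatment comparison: d = 0.78.
- Condition-by-time, post minus pre, baselines free: d = 0.78 / sqrt(2(1 − r)). At r = .5, .7, .8 this is 0.780, 1.007, 1.233.
- Posttreatment adjusted for baseline: d = 0.78 / sqrt(1 − r²), which is 0.901, 1.092, 1.300.
- Condition main effect over pre and post only: d = 0.39 / sqrt((1 + r)/2), which is 0.450, 0.423, 0.411.
- Condition main effect over seven visits (assumed weeks 0, 2, 4, 6, 8, 10, 22; equal correlation; effect weights 0, .2, .4, .6, .8, 1, 1, mean 4/7): d = 0.78 × (4/7) / sqrt((1 + 6r)/7), which is 0.590, 0.517, 0.490.

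| Analysis | r = .5 | r = .7 | r = .8 |
|---|---|---|---|
| Unadjusted posttreatment | 0.67 | 0.67 | 0.67 |
| Condition-by-time, free baselines | 0.67 | 0.87 | 0.97 |
| Posttreatment adjusted for baseline | 0.79 | 0.92 | 0.98 |
| Main effect, pre and post only | 0.28 | 0.26 | 0.24 |
| Main effect, seven visits, gradual effect | 0.44 | 0.36 | 0.33 |

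A simulation of the pre and post case with 4,000 runs at r = .5 and .7 gave 0.668 and 0.680 for the unadjusted comparison, 0.670 and 0.871 for condition-by-time, 0.786 and 0.914 for the adjusted contrast, and 0.293 and 0.271 for the main effect. These agree with the formulas.

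**Gain from adjustment.** Against the unadjusted comparison: 0.79 − 0.67 = 12 points up to 0.98 − 0.67 = 31 points. Against condition-by-time: 12, 5 and 1 points.

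**Sensitivity.** At r = .3 the adjusted contrast has 0.71, against 0.67 unadjusted and 0.53 for condition-by-time. At r = .88 the adjusted contrast and condition-by-time are level (0.999 and 0.998).

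**The case against.** The strongest reply is that nothing quoted is an error. A model that keeps pretreatment among the outcomes is sound if the test is condition-by-time, and it is about as efficient as covariate adjustment if the baseline means are held equal between arms. The surrounding text leans towards change: the next sentence describes changes in the symptom scales, the psychophysiology section compares baseline with postintervention, and Research Aims plans both between-group and within-group estimates. Covariates and contrasts are also commonly left to a full protocol or analysis plan, which is not shown, and the sentence on language does not claim to list every covariate.

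Most of this stands. A reader might infer that the condition test averages in the pretreatment score and so loses most of its power. The article does not say so, because it names no tested term. The 0.24 to 0.44 range belongs to that reading alone and further depends on the assumed visits and on the shape of the effect. If the full effect is present from week 2, the seven-visit main effect has power 0.78 at r = .5, close to the adjusted 0.79. At r = .3 it has 0.90, above the 0.71 of a single adjusted contrast, although it then estimates a different quantity.

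What the reply does not remove is that the article itself fixes the time points and gives an effect-size method with no use of baseline. On the two readings most favourable to the text, short of an unstated common-baseline model, adjustment still gains power for r of .5 to .8.

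**Conclusion.** The point holds as an available improvement, not as a demonstrated wrong analysis. The article leaves the DERS-16 treatment contrast unnamed and states the effect size without baseline adjustment, although the baseline score is collected. For a true difference of 0.78 SD with 20 per arm, adjustment raises power by 12 to 31 points over an unadjusted posttreatment comparison, and by 1 to 12 points over a condition-by-time contrast with free baselines. The sizes rest on an assumed pre-post correlation of .5 to .8, equal SDs and no dropout. The gain over condition-by-time is small when the correlation is high. The heavier loss from a main effect over all time points is only a possibility that the wording leaves open. It is a reason to name the contrast before data are seen, and no evidence that this test is planned.

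**What to change.** State in Analyses for Rating Scales that the DERS-16 treatment effect is the condition contrast at week 10 to 11, from a mixed model with condition, time and condition-by-time. Baseline DERS-16 enters either as a covariate with postrandomisation scores as outcomes, or as an outcome with baseline means constrained equal between arms. Report the effect size from this adjusted contrast, scaled by the baseline SD, with its 95% CI, in place of the plain Cohen d or nonparametric test.

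The cost is a change of wording and one degree of freedom. No new data are needed.
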